## ABSTRACT

Despite a large decline in new adult HIV infections in eastern and southern Africa from 2005-2015, progress has slowed in recent years and multiple disparities have persisted within countries and between men and women. In particular, HIV risk among adolescent girls and young women in the region remains extremely high. Transactional sex, or the exchange of material support or goods in non-commercial sexual relationships that are often age-disparate, is widely believed to be among the main driving factors for the HIV risk in this population. Although various structural and biomedical HIV prevention interventions have targeted adolescent girls and young women, there is a large gap when it comes to interventions targeting men who engage in transactional sex. The proposed pilot project seeks to fill this important gap by using behavioral economics principles to promote savings and shift money from high-risk activities toward saving for the future.

The project will assess the acceptability, feasibility, and potential impact of a novel prize-linked savings intervention designed to shift men's income away from alcohol and transactional sex and towards saving for the future. Prize-linked savings accounts have been in existence for many years in some countries and they offer savers a random, lottery-like payout proportional to the amount participants save, instead of traditional interest income. A number of banks, employers, and policymakers have recently promoted this low-cost, scalable approach to increasing savings among low-income individuals. However, there have been no assessments of whether prize-linked savings interventions can induce changes in not only economic behaviors like savings but also key health-related behaviors. We will conduct a pilot randomized trial among men in Kenya to assess whether offering prize-linked savings opportunities leads to reduced spending on alcohol and transactional sex. In addition, we will explore whether the intervention leads to reduced financial stress and builds future-orientation among men – all of which could lead to reduced risk-taking behavior. The project will enroll men who in communities with high HIV risk, randomize them to the savings intervention, and assess changes in key economic and self-reported health outcomes over a 3-6 month period with baseline and follow-up surveys. Findings from the pilot trial may reveal new ways to influence the HIV epidemic in priority regions where it continues unabated and will directly inform the design of a larger-scale study that focused on ways to achieve changes in health and economic behaviors.

## **LIST OF ACRONYMS**

HIV: Human immunodeficiency virus  
AGYW: Adolescent girls and young women  
AIDS: Acquired immune deficiency syndrome  
ATM: Automatic teller machine  
PEPFAR: President's emergency program for AIDS relief  
SMS: Short message service  
IPA: Innovations for Poverty Action  
PI: Principal investigator  
IRB: Institutional review board  
NIH: National Institutes of Health  
USD: U.S. dollar

## 1.0 BACKGROUND

**Transactional sex is among the main factors behind high HIV incidence in parts of eastern and southern Africa and among adolescent girls and young women (AGYW) in particular.[1-3]** The intensity of the HIV epidemic in Kenya's Nyanza region – particularly in communities along Lake Victoria shorelines and islands – warrants a combination of biomedical and behavioral interventions. From the beginning of the epidemic in Africa, HIV/AIDS has been concentrated in Lake Victoria fishing communities in Kenya, Tanzania and Uganda. HIV incidence rates remain persistently high in these communities despite progress against the spread of HIV in the region overall.[3-5] Transactional sex, venue-based commercial sex work, and alcohol consumption, which occur at elevated rates in the region[4-6] are important contributors to the continued spread of HIV. The risk of HIV acquisition by AGYW is further enhanced by the age of their sexual partners being substantially higher. *This study is significant because it will explore an approach whose goal is to achieve sexual behavior change among men in communities with continued high rates of HIV.*

**Policies to address HIV risk among AGYW have largely focused on achieving behavior change among them or providing essential services to them, but have neglected to address the role played by men's demand for transactional sex with AGYW.** When men are targeted with HIV prevention services, the focus has been on increasing their uptake of voluntary medical male circumcision and HIV testing, and linking those who are HIV-positive to treatment, rather than focusing on what motivates their sexual behavior. *This study will address a missing element of prevention efforts in regions with a high prevalence of transactional sex by deploying a behavioral economics intervention to shift spending away from high-risk activities like transactional sex among men.*

**The rapid expansion of mobile phone ownership in Africa has also led to increased access to financial services among the poor.** In the past 10 years, mobile phone companies began to offer a “mobile money” service in which people who own a cell phone number could deposit, withdraw and transfer money simply by visiting a local “cash point” (in rural areas, this is typically a kiosk in villages). Essentially, this made it easier for individuals to save money and send money to each other, with kiosks where people typically buy vouchers to top up their phone credit serving as bank branches. Use of mobile money services is now ubiquitous in Kenya due to the early introduction of the *M-Pesa* service by Safaricom, a leading mobile phone company.[7, 8] The services were used by 96% of Kenyan households and there were 110,000 “cash points” in the country (as compared to only 2,700 bank ATMs). Mobile money is now widely used in nearly all developing countries.[9] A recent study in *Science* showed that expansion of mobile money in Kenya contributed significantly to poverty alleviation, and that it led to increased financial resilience and occupational choice.[7] This expansion of mobile phone ownership and mobile money has induced banks to provide a wider array of savings products targeted at previously unbanked individuals and communities. Many banks now offer savings accounts in which deposits and withdrawals can be made by using mobile money, rather than visiting physical branch offices of the banks.

**With the widespread availability of savings accounts in Kenya and other countries, there is an opportunity to deploy novel interventions that promote public health objectives.** To our knowledge, no studies have sought to use savings accounts to influence men's spending on risk factors for HIV such as alcohol and transactional sex. *We propose to use prize-linked savings accounts as a vehicle for a novel intervention that will encourage men to alter their expenditure patterns and save more money.* Our theoretical rationale is that when offered incentives to save money, men will save more of their income and spend less on alcohol and transactional sex. There are other ways in which incentivizing saving may reduce sexual risk

behavior. Lower spending on alcohol itself can reduce sexual risk-taking since alcohol is a known risk factor. Men may also increase their consideration of future health and well-being when they start to save money. Our idea builds on prior research showing that poverty alone does not explain why the poor save very little of their income. Instead, behavioral factors including a lack of incentives for saving have been noted as a key reason.[10, 11]

**Behavioral economics provide a strong rationale for using lottery incentives to promote various health and economic behaviors.** Insights from psychology and economics point to various factors and decision-making biases that make lottery incentives a valuable strategy for motivating individuals to adopt certain behaviors.[12] As seminal behavioral economic research of Kahneman and Tversky has shown, people tend to overestimate small probabilities,[13] implying that lotteries with low probabilities of winning large prizes are very effective in motivating individuals. Lotteries used as incentives have been successful at altering various health behaviors and they remain popular among many individuals in the U.S. and abroad. *Given the proven ability of lottery incentives and rewards to motivate individuals generally, it is likely that lottery incentives linked to savings amounts will encourage men to save a greater portion of their income on a regular basis.*

**“Prize-linked savings” accounts exist in several countries and have generally succeeded in boosting individuals’ savings.** Prize-linked savings accounts typically offer savers a random, lottery-like payout in the form of cash or goods instead of traditional interest income.[14, 15] The probability of winning prizes is usually determined by the amount of new deposits made each month, meaning that individuals’ chances of winning a prize go up as they save more each month. A recent study in South Africa showed that prize-linked savings accounts were attractive to a broad group of individuals, but *especially* to those who did not previously save money and to those with a greater tendency to take risks.[16] In South Africa, the prize-linked savings account added a fun, “gaming” element to saving money and increased total amounts saved by 38%. Based on the popularity of such accounts globally,[17] there is reason to believe that Kenyan men will have considerable interest in saving more of their income if offered a lottery-like incentives to do so. *Thus, targeting income-earning men with incentive to save money (and accordingly, disincentives to spend money on transactional sex) has as-yet untested potential to serve as an effective risk-reducing intervention among men.* This study will focus on men engaged in fishing and transport industries in communities with low savings rates. These individuals may be responsive to a savings intervention because they earn money on a daily basis and thus have cash available, a pre-requisite to saving. The structure of the prize-linked savings intervention may be especially relevant to these men, who are generally younger and whose occupations involve risk-taking, and who thus may be interested in the risky, lottery-style prizes.

## 2.0 JUSTIFICATION and AIMS

The proposed pilot project seeks to fill a large gap in the development and evaluation of interventions targeting the men who engage in transactional sex with AGYW and other high-risk HIV behaviors. Applying concepts from behavioral economics we will explore the acceptability and feasibility of a prize-linked savings intervention designed to encourage men to reduce spending on alcohol and transactional sex and increase savings for the future. The intervention is intended to offer men an incentive to shift their spending toward saving for the future, and therefore away from certain behaviors (like alcohol use and transactional sex) which put them at high risk for HIV acquisition and transmission. Given the promise of prize-linked savings intervention as well as the paucity of interventions that target men and seek to reduce their demand for transactional sex, the proposed pilot project has the potential to represent an

exploratory step in a new and important direction. This pilot project will generate preliminary data necessary for designing a well-powered randomized controlled trial of a savings intervention designed to reduce men's engagement in transactional sex and lower their HIV risk and the associated risk to AGYW.

The primary aim of the project is to conduct a pilot randomized trial of a prize-linked savings intervention to promote savings behavior among up to 300 high-risk men in Siaya, Kenya. We will assess changes in financial savings and expenditures on key items of interest from the perspective of HIV risk (alcohol use, gifts and transfers to sexual partners, and sexual behavior) in order to evaluate the likely effectiveness of the intervention. This data will provide preliminary information on feasibility and acceptability of the intervention in order to develop a larger trial of the prize-linked savings intervention. The project may also include a qualitative component to gain further insights on acceptability and impact of the intervention.

### **3.0 STUDY DESIGN**

#### **3.1 Overview of study design**

We will develop a researcher-implemented prize-linked savings intervention that is linked to participants' savings account balances. We will develop a system of lottery-based rewards that participants can win depending on how much their account balance goes up (e.g. for every 100 Ksh by which savings increases, participants get an entry into a lottery in which there is a chance of winning monetary rewards). We may also consider other ways to structure rewards for saving and explore the potential for interventions to build future-orientation among men. Participants in the study will be randomized to a control group or an intervention group that receives the prize-linked savings intervention.

#### **3.2 Study sites**

The study will be conducted in communities in Siaya County, Kenya, where HIV prevalence was estimated to be 24.6% in 2014[18]. A recent study[19] from Siaya County reported that adult HIV prevalence in the Gem subarea of Siaya County was 15%. This prevalence remains well above the national HIV prevalence, however, making it a priority area for this study. Siaya County is part of the populous Nyanza region, which has been the focus of Kenya's HIV prevention efforts and those of donors like PEPFAR. The high HIV incidence – particularly among AGYW – and the contribution of transactional sex to the epidemic in this region has been widely documented.[20-22]

#### **3.3 Study population**

The target population will be men who work in fishing and other informal sector jobs such as public transport and *jua-kali* (artisans).

### **4.0 RANDOMIZED TRIAL PROCEDURES**

#### **4.1 Recruitment**

Working in ~2-5 shoreline communities in Siaya County, trained research assistants will identify potential participants and will conduct a short set of screening questions to determine eligibility prior to obtaining informed consent. These questions will obtain information on men's occupation since existing research indicates that those who earn income on a regular basis (fishermen, transportation worker, and other laborers) are more likely to have multiple sexual partnerships, including some that have a transactional element. Eligible individuals will be recruited immediately following the screening questions. We will seek to enroll about 300 men who meet study eligibility criteria.

## **4.2 Eligibility criteria**

This study will focus on an intervention aimed at changing savings and expenditure patterns, and risk behaviors, among men in communities with high prevalence of transactional sex. Thus we will exclusively recruit men in the pilot phase.

Inclusion criteria:

1. Resident in selected shoreline communities in Siaya County, Kenya
2. Male
3. Age 21 years and above
4. Primary or secondary occupation is fishing or transportation (i.e. motorbike taxi driver)
5. Owns mobile phone
6. Is willing to open a savings account with a local bank

Exclusion criteria:

1. Planning to relocate from study communities in the next 6 months
2. Does not express willingness to open a savings account

## **4.3 Consent and enrollment processes**

Participants eligible for enrollment in the study will be approached by the study team at the time of the baseline survey and will complete an informed consent procedure immediately prior to the baseline survey. The informed consent form will be distributed to potential participants and will be read aloud (in English, Swahili or Dholuo depending on participant's preference). Survey staff will respond to questions and offer further explanations where necessary, and will ask participants to sign the consent form (or to make a mark, in the case of respondents who cannot write.) For those desiring more time to make a decision, survey staff will leave the consent document with the potential respondent and will follow up on a subsequent day.

Following enrollment in the study, a baseline questionnaire will be administered to all participants (described below). All participants will then be asked to open a savings account with a local banking partner, a process that the study will facilitate. There will be no out-of-pocket cost for participants to open an account and there will be no requirement to deposit their own money into the account.

## **4.4 Randomization procedures**

Participants will be randomly assigned to either an intervention or control group using simple random assignment. Individuals meeting eligibility criteria and providing consent will be randomized in equal proportions to one of two groups, a control group or an intervention group that receives the prize-linked savings intervention.

## **4.5 Intervention group**

Research assistant will explain the structure of the lottery prizes to participants randomized to the lottery incentive group. Participants will be told their chance of winning monetary rewards will be based on the amount by which their account balance goes up (e.g. for every 100 Ksh by which savings increases, participants get an entry into a lottery for monetary rewards.) This type of prize-linked savings intervention has been shown to promote savings in other settings. During the intervention period, participants' savings account activity will be checked at regular intervals and lottery prizes will be determined at these intervals. Participants will learn about the lottery outcome via SMS and prizes will be deposited directly into their savings accounts.

Other intervention components may include education materials to explain how the prize-linked savings incentives work and that emphasize the potential benefits of saving money (having greater ability to cope with setbacks, build or upgrade their homes, pay school fees, buy farm

inputs, buy more motorbikes for use in business, or start a different business; etc.). Participants in the intervention group will be encouraged to have more consideration for their future health and economic status, as this may motivate them to save more money. They will also be encouraged to consider the opportunity and health cost of their expenditures on alcohol and transactional sex and not miss the opportunity to win prizes by saving money.

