#### **4.6 Comparison group**

During the study period, participants' savings account activity will also be tracked at regular intervals, but they will not be eligible to receive lottery-style prizes. They may instead receive interest on the amount they have saved at a standard rate that is determined by the banking partner.

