#### **4.7 Data collection activities**

Structured questionnaires will be administered to all participants at the time of enrollment (baseline) and at study completion. Data will be collected by a team from Innovations for Poverty Action (IPA), which has led a number of household surveys in the Nyanza region. Trained research assistants from IPA will administer these questionnaires using tablet computers. Participants will receive a small amount of compensation for the time required to complete each survey.

*Baseline data collection:* A baseline questionnaire will collect information on demographic characteristics, employment and income, assets and savings, consumption and expenditures, self-reported sexual behavior, alcohol and substance use, HIV risk perceptions, and questions about financial stress, future orientation, and expectations. Sexual behavior questions will inquire about past engagement in transactional sex (defined broadly to include financial and non-financial transfers from the partner to the woman, approximate age of sexual partners).

*Interim data collection:* Additional contact from the survey team may occur at regular intervals during the intervention period. These intermittent contacts may occur via SMS or in person and are expected to take only a few minutes.

*Endline data collection:* An endline survey with similar content as the baseline will be administered about 3-4 months after study enrollment in order to measure economic and health outcomes that have the potential to be affected by the intervention..

The questionnaire modules will be based on questionnaires that have been used in other studies in the Nyanza region and on surveys such as the Demographic and Health Survey and the World Bank's Living Standards Measurement Surveys.

*Qualitative interviews:* In addition to the baseline and endline surveys, we may conduct in-depth interviews with up to 20 men to explore perceptions of the prize-linked savings intervention. Beyond exploring the extent to which the intervention motivated men to save money and change their health and economic behavior, the interviews will also assess other factors that influence men's decisions – including barriers to saving such as beliefs about mortality risks in the future.

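### Messages on future planning, alcohol and transactional sex are planned for the intervention arm only, so effects on primary outcomes 3–5 and on future orientation belong to the package and not to the prizes

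*Protocol*

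**What the plan says.** **The question.** The Abstract says the trial will "assess whether offering prize-linked savings opportunities leads to reduced spending on alcohol and transactional sex". Section 1.0 gives the rationale: an incentive to save leads men to save more and so to spend less on alcohol and transactional sex. It adds that men may think more about future health once they begin to save. The Abstract also lists future orientation among the things to be explored.

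**The intervention arm (section 4.5).** Besides the lottery, two components are stated firmly:
- "Participants in the intervention group will be encouraged to have more consideration for their future health and economic status"
- "They will also be encouraged to consider the opportunity and health cost of their expenditures on alcohol and transactional sex"

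A third is only possible: "Other intervention components may include education materials to explain how the prize-linked savings incentives work".

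**The control arm (section 4.6).** Their "savings account activity will also be tracked at regular intervals, but they will not be eligible to receive lottery-style prizes"; they may earn ordinary bank interest. No encouragement or messaging is described for them.

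**Design and outcomes.** Section 4.4 has two arms in equal proportions. Section 4.8 lists alcohol expenditure, participation in transactional sex and expenditure on transactional sex as primary outcomes 3, 4 and 5. Section 6.0 accepts that some outcomes, such as sexual behaviour, are self-reported, and treats this as no great problem because both groups are measured.

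**The concern.** The messages name the behaviours that outcomes 3–5 measure. If the intervention arm reports less drinking or less transactional sex, the cause could be the prizes, the messages or both, and with two arms no analysis can separate them.

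The same applies to the proposed mechanism. Section 1.0 expects saving to make men more future-oriented, but section 4.5 has staff encourage that directly. A change in future orientation would not show that saving produced it.

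There is also a measurement problem. Men whom the study has urged to weigh the cost of alcohol and transactional sex may report less of either without changing their behaviour.

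The pilot is meant to inform the design of a larger trial. If a message effect is read as a prize effect, that trial would be built on the wrong component.

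**Working it through.** **1. Components side by side**

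| Component | Intervention (4.5) | Control (4.6) | Status |
|---|---|---|---|
| Facilitated savings account (4.3) | yes | yes | common to both |
| Account tracking | yes | yes | common to both |
| Lottery prizes and SMS notice of the result | yes | no | the prize and its delivery |
| Encouragement to consider future health and finances | yes | none described | firm |
| Encouragement to weigh the cost of alcohol and transactional sex | yes | none described | firm |
| Education materials | possible | none described | optional |
| Interim contact by SMS or in person (4.7) | possible | possible | optional, not tied to an arm |

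Two firm components other than the prize differ between the arms.

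**2. What the contrast estimates.** Let Y(p, m) be the mean outcome with prizes p and messages m, each 0 or 1. The trial estimates Y(1,1) − Y(0,0). This equals [Y(1,1) − Y(0,1)] + [Y(0,1) − Y(0,0)], the effect of prizes given messages plus the effect of messages alone. The Abstract's question concerns prizes. Neither term can be estimated by itself, because no arm has messages without prizes or prizes without messages.

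**3. Self-report.** Write each arm's reported mean as its true mean plus a reporting error: b1 in the intervention arm, b0 in the control arm. The reported difference is the true difference plus (b1 − b0). Measuring both arms removes the error only if b1 = b0. Messages given to one arm are a reason to doubt that equality.

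**4. The plan's own power figures (section 4.9b).** These are reproduced first to fix the method: two-sided α = 0.05, equal arms, pooled-variance normal approximation, no continuity correction.

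Power = Φ[(d − 1.96·s0)/s1], with s0 = √(2p̄(1−p̄)/n) and s1 = √(p1(1−p1)/n + p2(1−p2)/n).

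- 10% against 25%, n = 100 per arm: s0 = 0.0537, s1 = 0.0527, (0.15 − 0.1053)/0.0527 = 0.85, power 80.2%. The stated N = 200 is confirmed.
- 50% against 66%, n = 150 per arm: s0 = 0.0570, s1 = 0.0562, (0.16 − 0.1117)/0.0562 = 0.86, power 80.5%. The stated 16 points at N = 300 is confirmed.

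**5. Illustration with assumed rates that are not in the protocol.** Suppose prizes do nothing and messages alone lower a reported binary behaviour, with 150 men per arm. For 50% against 40%: s0 = 0.0574, s1 = 0.0572, (0.10 − 0.1126)/0.0572 = −0.22, so the chance of a significant difference is 41%. The full range is:

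| Drop due to messages alone | Control rate 50% | Control rate 30% |
|---|---|---|
| 5 points | 14% | 16% |
| 10 points | 41% | 52% |
| 15 points | 75% | 88% |
| 20 points | 95% | 99% |

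The document gives no basis for choosing a row. The table shows only that a message or reporting effect of moderate size could produce a significant result at this sample size.

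**The case against.** The strongest reply is that the trial tests an intervention with several parts. Section 4.5 places the education under other components, section 3.1 allows for building future orientation, and section 2.0 speaks of the likely effectiveness of the intervention. Package against plain account is a valid randomised contrast and a reasonable aim for a pilot. The sentence on alcohol and transactional sex also ends by reminding men not to miss the chance of a prize, so the message is tied to the offer, and no counselling sessions or amount of contact are described. All of this stands. It supports a package conclusion, but the Abstract and section 1.0 frame the question and mechanism around the savings incentive.

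A reader might infer more than the document supports:

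- **That only the intervention arm has regular SMS contact.** The one SMS specific to that arm reports the lottery result: "Participants will learn about the lottery outcome via SMS and prizes will be deposited directly into their savings accounts". It is part of delivering the prize. Of the optional interim contacts, section 4.7 says "These intermittent contacts may occur via SMS or in person and are expected to take only a few minutes" and does not limit them to one arm. An argument that SMS reminders confound outcomes 1–2 therefore fails.
- **That savings education is a fixed difference between arms.** It is optional, and partly explains the prize scheme, which would mean nothing to controls.
- **That no outcome at all can be interpreted.** The messages on alcohol and transactional sex bear on outcomes 3–5, and the encouragement about the future on future orientation. The case does not extend to every outcome.
- **That the protocol claims to test prizes alone.** It nowhere says so.

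**Conclusion.** The point holds for primary outcomes 3–5 and for future orientation. For these, the trial can estimate the effect of prizes plus messaging against a plain account. It cannot attribute a difference to offering prize-linked savings or to saving itself. For self-reported outcomes, section 6.0 is also wrong to treat measurement in both arms as sufficient, because the messaging may make reporting differ by arm.

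The share due to each component cannot be identified from this design, so no size can be put on it. The 14% to 99% range above rests on assumed rates and shows plausibility only.

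The conclusion assumes that controls receive no equivalent messages. Section 4.6 describes none, but it does not expressly rule them out.

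**What to change.** 1. In the Abstract and section 2.0, restate the objective for outcomes 3–5 and future orientation as the effect of prize-linked savings plus future-orientation and risk messaging, compared with a plain savings account. Word the planned conclusions the same way, without crediting the prizes or saving itself.
2. In section 6.0, replace the statement on self-report with an acknowledgement that messaging given to one arm may cause differential reporting, which measuring both groups does not remove.

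Both are wording changes. The cost is a less specific claim about the prizes.

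Giving controls the same messages is an alternative for the sponsor to weigh. It would bring the contrast closer to prizes alone but may narrow it, including on outcome 1, on which the sample size is based. As an assumed example with 150 per arm, suppose the control rate rose from 50% to 55% while the intervention rate stayed at 66%. Then s0 = 0.0564, s1 = 0.0561 and (0.11 − 0.1106)/0.0561 = −0.01, so power would fall from about 80% to about 50%. A message-only arm would also separate the components, but at the price of more participants.
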